### Sample size

Variability was estimated from the feasibility study.
^24^ Estimates of the standard deviation (SD) for systolic BP change from baseline at 4-weeks, 3 and 6-months were 12.5, 10.8 and 14.4 mmHg respectively. With a minimal clinical important difference 5 mmHg and SD of 14.4, we require 352 participants to complete this study to attain 90% power with a 5% significance level. Assuming 35% attrition we aim to randomise 542 participants, 271 in each group. The sample size confidence interval has been calculated using Pass11 software (PASS 11. NCSS, LLC. Kaysville, Utah, USA.
www.ncss.com).

For qualitative data samples, we will conduct up to four online focus groups of 6–8 participants each from the intervention group plus up to 15 interviews with stakeholders – it is expected that this sample will achieve data saturation whereby no new qualitative data codes/elements are identified when approaching the full sample.
^25^

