Participants will receive electronic reminders (email, text or WhatsApp message depending on participant preference) ahead of each follow up time point to prompt data collection. They will receive further reminders on the day of assessment and then daily during the submission window (refer to above) to submit their information through the online questionnaire. Intervention arm participants will receive reminders of exercise sessions as per their preferences set during baseline data collection. Weekly motivational messages will also be sent to control participants for the first 6 weeks of the study. This will aid adherence to the study and IE training and reminders will include a link to input their data each time or at regular weekly intervals. At each follow up, participants will record their home blood pressure, heart rate readings and in their participant diary and submit these via an online questionnaire using a link emailed or texted to participants. Alternative methods for data recording will be made available to participants where requested, for accessibility (telephone call, on paper etc.) and supported by local teams or the study team centrally.

The protocol requires three consecutive measurements (separated by two minutes) always using the same arm (use arm with high reading if >15 mmHg difference when first checked), to be taken in the morning and afternoon for three days at each timepoint. Home blood pressure monitoring will follow NICE and ESH/ESC guidelines
^1^
^,^
^26^ using a British and Irish Hypertension Society approved blood pressure monitor. Participants will be asked to keep their chosen times of blood pressure measurements and ingestion of medication consistent throughout the study. Adverse events, checking of medication, adapted version of UK EPIC NORFOLK Food Frequency Questionnaire,
^34^ General Practice Physical Activity Questionnaire,
^35^ EuroQOL quality of life 5D-5L questionnaire,
^36^ study-specific IE intervention experience questionnaire (intervention group only at week 4) and health economics data (questionnaire adapted for the study from
^37^) will also be collected according to the schedule of assessments (

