The ISOFITTER study steering committee is chaired by [name] (Chair of the British and Irish Hypertension Society Collaborative Research Standing Committee). The steering committee is composed of at least 75% members who are independent to the study team. The committee includes the Chief Investigators, an independent statistician and health economist, clinicians with expertise in hypertension/clinical trials, an exercise specialist, an expert in qualitative health services research, an implementation specialist and two independent lay members. The committee critically oversees progress, outputs, deliverables and governance of the project. The delivery of the study is managed by the East Kent Clinical Trials Unit (CTU). A project management group brings together the CTU and the academic delivery team from the University of Kent and Canterbury Christ Church University. A research inclusion subcommittee, chaired by [name] [name] as a public co-applicant on the study, oversees recruitment of a representative study sample, ensuring inclusion of participant groups commonly under-represented in research such as those on low income and those from minority ethnic groups.

**
*Adverse event monitoring*
**

For the purpose of this study an adverse event (AE) is defined as any untoward medical occurrence in a study participant, whereas a serious adverse event (SAE) is any untoward medical occurrence that results in death, is life-threatening at the time of the event, requires participant hospitalisation or prolongation of existing hospitalisation, results in persistent or significant disability/incapacity, or consists of a congenital anomaly or birth defect. Other ‘important medical events’ may also be considered serious if they jeopardise the participant or require an intervention to prevent one of the above consequences. Only AEs or SAEs which might have resulted (definitely or probably) from the study intervention, e.g. muscular injury in the leg as a result of IE, will be recorded. These will be submitted by the participant in their assessment questionnaires. The CTU will monitor reported AEs from participants and report any AEs or SAEs as following standard governance processes and requirements.

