Common wall squat related adverse events would be similar in nature to other forms of recommended exercise (e.g. aerobic exercise or strength training) and may include muscle soreness after exercise, stress on joints (particularly the knees and ankles), dizziness during or after exercise, blood pressure spikes if holding of breath occurs during exercise (instructions to breath normally is including in the instructions to participants) and potential post-exercise hypotension. These will be recorded throughout the study.

In the event of an Adverse Event (AE) or Serious Adverse Event (SAE) the clinical lead applicant would be unblinded to the participant’s randomisation group to allow them to assess the relatedness of the event to the intervention. This information would be available on the data collection questionnaire/forms stored centrally in the trial master file. This information would be shared by the delivery team only when necessary.

Although IE can be undertaken in pregnancy, we have decided to take a conservative approach and exclude pregnant participants. Any women of childbearing potential should agree to use a medically accepted method of contraception while they are participating in the study. Should a participant get pregnant during the study, they will be asked to notify the study team within 7 days of becoming aware of the pregnancy. In case of a pregnancy while receiving study treatment, a participant should be withdrawn from the study.

**
*Data monitoring and audit*
**

Only the CTU delivery team will have access to the full dataset throughout the study. The statistician and research team will have access to an anonymised data set for analysis. Upon completion of analysis, the anonymised data will be available to other researchers upon reasonable written request with clearly defined purpose and its use will be to benefit of the wider society (see section 7).

Study data will be collected and managed using REDCap electronic data capture tools
^49^
^,^

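### The one route the article names for adverse and serious adverse events is the scheduled questionnaire, so the study may learn of a serious event three to six months late, or never

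*Protocol article*

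**What the plan says.** In the Protocol article, Study governance, Adverse event monitoring, the SAE definition includes death, life-threatening events and hospitalisation. Recording is limited: "Only AEs or SAEs which might have resulted (definitely or probably) from the study intervention". The intake route follows: "These will be submitted by the participant in their assessment questionnaires". The clinical trials unit then monitors what participants have reported and passes it on through its usual governance processes.

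The same section lists common events expected with wall squats (muscle soreness, joint stress, dizziness, blood pressure spikes, post-exercise hypotension) and says: "These will be recorded throughout the study". For pregnancy, participants have a deadline: "they will be asked to notify the study team within 7 days of becoming aware of the pregnancy".

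Under Participant on study timeline and assessments, the list of follow-up data begins "Adverse events, checking of medication, adapted version of UK EPIC NORFOLK Food Frequency Questionnaire" and ends by saying that these items "will also be collected according to the schedule of assessments", with a pointer to Table 1. That table sets follow-up at Day 30 (±3 days), Month 3 and Month 6 (±7 days each), and Month 12 (±7 days) for 50 intervention participants. It has no AE row.

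Data monitoring and audit explains that there is no data monitoring committee. The reasons are a low-risk assessment and monthly reporting to the Project Management Group; the steering committee receives data quarterly.

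**The concern.** The exercise is unsupervised and done at home, so the study sees no event unless someone reports it. A form that comes three or four times is a weak instrument for brief events tied to single sessions, such as dizziness, and a slow one for serious events. It is also selective. People who stop returning forms because something went wrong are those whose events are least likely to be recorded. If that happens, the safety account of the trial leans in favour of the exercise, and those overseeing the trial review data that cannot yet contain the event.

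**Working it through.** The article states no reporting delay, so there is no figure to reproduce. The delay follows from the assessment schedule.

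**Inputs** (Table 1 and the follow-up section): assessments at Day 0, Day 30 (±3), Month 3 (±7), Month 6 (±7) and Month 12 (±7, 50 people). One month is taken as 365.25 / 12 = 30.44 days, so Month 3 is day 91.3, Month 6 is day 182.6 and Month 12 is day 365.25.

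**Formulas.** Nominal gap = next assessment minus previous assessment. Longest gap within windows = nominal gap + window of the previous form + window of the next form (previous form at its earliest, next at its latest).

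| Interval | Nominal gap (days) | Longest gap (days) |
|---|---|---|
| Baseline to Day 30 | 30 − 0 = 30 | 30 + 0 + 3 = 33 |
| Day 30 to Month 3 | 91.3 − 30 = 61.3 | 61.3 + 3 + 7 = 71.3 |
| Month 3 to Month 6 | 182.6 − 91.3 = 91.3 | 91.3 + 7 + 7 = 105.3 |
| Month 6 to Month 12 (n = 50) | 365.25 − 182.6 = 182.6 | 182.6 + 7 + 7 = 196.6 |

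These are waits for an event soon after a form. If an event is equally likely on any day of the interval, the mean wait is half the nominal gap: 91.3 / 2 = about 46 days after Month 3, and 182.6 / 2 = about 91 days after Month 6.

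**The statements side by side.**

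- *Recorded throughout the study* against *submitted in the assessment questionnaires*: the first implies continuous capture, while the second names an instrument that comes three times, or four for 50 people.
- *AEs collected according to Table 1* against *Table 1*: the table lists the other items but gives no time for AEs.
- *Pregnancy within 7 days* against *SAEs*: the authors wrote an event-driven, time-limited rule for one occurrence and none for hospitalisation or a life-threatening event.
- *Monthly review in place of a data monitoring committee* against the gaps above: 91.3 / 30.44 = 3 monthly reports can pass between Month 3 and Month 6, and 182.6 / 30.44 = 6 between Month 6 and Month 12, before a form that could show the event is due.
- *SAE definition includes death* against *submitted by the participant*: a fatal event cannot arrive by this route.

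**Participants who stop responding.** The withdrawal section deals with data collected up to withdrawal. No section describes a safety contact afterwards or after a missed form. The Sample size section plans for such losses: "Assuming 35% attrition we aim to randomise 542 participants, 271 in each group".

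**The case against.** The strongest reply is that the article names one route without calling it exclusive. It is also a condensed account, and the full protocol and data collection tools are said to be in a public repository. Notification deadlines and withdrawal forms are often left to such documents. There is a telephone support line in office hours. For exercise sessions, "reminders will include a link to input their data each time or at regular weekly intervals". The trials unit follows standard governance processes.

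Part of this stands: a reader might infer that no faster route exists anywhere, and the article cannot show that. But the point does not rest on silence. The article makes a positive statement about how SAEs are submitted. The telephone line is offered as general support, the session link is not assigned to AEs, and the governance sentence concerns events already reported. None of them corrects the stated route.

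A reader might also infer that nobody can act on a serious event in time. The documents contradict this: the GP or hospital remains responsible for care, GPs are told of participation by letter, and participants are advised to seek GP care if their condition changes.

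Nor does stopping the exercise mean leaving the study. The analysis is by intention to treat, and reminders go out daily in each submission window, so someone who stops is still asked for data. The risk of loss concerns those who stop returning forms.

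The low-risk assessment is a stated reason for having no data monitoring committee, and such a committee would not by itself shorten the path from participant to trials unit. The point here is narrower: the monthly review cited as a safeguard depends on how quickly events come in.

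**Conclusion.** The point holds and should be acted on. As the article stands, the study may learn of a serious event about three months late between Month 3 and Month 6 (nominal 91 days, at most about 105). In the 50-person 12-month group the delay may be about six months (nominal 183, at most about 197). It may not learn of the event at all from someone who stops returning forms or dies. The maxima need opposite edges of two windows. All figures assume that the questionnaire is the route actually used.

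Two further inferences are not supported. A reader might multiply 35% by 271 and conclude that about 95 intervention participants leave with events unreported. The 35% is a sample-size allowance for non-completion; it does not say how many of those people had an event, or when they left relative to their last form. A reader might also expect a biased comparison of AE rates between arms. The article lists no such outcome, and a rule that records only events judged definitely or probably due to the intervention does not lend itself to one. The possible bias is in the description of how safe the exercise is. No sample-size or error-rate figure is affected.

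**What to change.** Reconcile the Adverse event monitoring section, the follow-up section and Table 1:

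1. State an event-driven, time-limited route for SAEs to reach the trials unit, through the existing telephone line or REDCap, in addition to the questionnaires. It should also accept a report from someone other than the participant. If the full protocol already has such a route, correct the article to describe it; no amendment is then needed on this item.
2. Send a short form on AEs and the reason for stopping to anyone who withdraws or misses an assessment window.
3. Add an AE row to Table 1 at Day 30, Month 3, Month 6 and Month 12.

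Optionally, add one AE alert item to the data link that intervention participants already receive.

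The cost is a few REDCap fields, a protocol amendment where the procedure changes, and some extra reports to triage.

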## Public and patient involvement

The study is being delivered using co-production principles with members of the public with or without lived experience of hypertension. Three public co-applicants have been involved with the study from early design stages, including methodology and objectives, through to set up and delivery. Contributions included co-designing the participant intervention resources, co-design of the study website, decisions on recruitment strategies for inclusivity and reviewing of this protocol and other study related documentation. An additional two public members sit on the Trial Steering Committee. A further group of public members assist with ad hoc requests and document reviews. The public advisory team continue to support with reviewing study processes, documentation, recruitment and ongoing management including monitoring risks. Furthermore, they will support with the participant focus groups, qualitative analysis and review of lay summaries. Our public co-applicants also sit on our Research Inclusion Committee, chaired by one of the public co-applicants chairs this 6-weekly panel.

## Conclusion

The ISOFITTER study will establish whether self-administered, home-based wall squat isometric exercise in addition to standard lifestyle advice lowers blood pressure by 5 mmHg in people with uncomplicated stage 1 and 2 hypertension with or without a single blood pressure agent. It will provide implementation evidence to support patients to adhere over the long term, context for scaling up of the intervention and its cost.

## Consent to publish

Consent to publish a persons image in
Figure 1 has been obtained for the purposes of publishing this article. No other identifiable information is included in this article.

## Data Availability

On study completion and publication, access to an anonymised data set will be available where the sharing of data has a clearly defined purpose and its use will be of benefit to wider society in line with UK policies.
^51^ When available, data can be found in the study external repository which is in the public domain
^52^. Data that will be made available includes:
oAnonymised quantitative study data where participants have consented to use for future researchoQualitative study data where participants have opted in to the use of their data for future research. Anonymised quantitative study data where participants have consented to use for future research Qualitative study data where participants have opted in to the use of their data for future research. Open Science Framework. Randomised controlled effectiveness study of isometric exercise (IE) in adults with stage 1 and 2 hypertension (ISOFITTER study). Project identifier: DOI
http://dx.doi.org/10.17605/OSF.IO/QHFBW Dataset weblink:
OSF | Randomised controlled effectiveness study of isometric exercise (IE) in adults with stage 1 and 2 hypertension (ISOFITTER study)
^48^ This project contains the following underlying data:
•Protocol paper supplementary documents – contains the SPIRIT 2 checklist for protocol paper publication.•Study documentation: Contains all study documentation including protocol, participant facing documents and data collection tools•Study Data Analysis Plan•On study completion, this repository will contain a folder with fully anonymised study data once analysis is completed. Protocol paper supplementary documents – contains the SPIRIT 2 checklist for protocol paper publication. Study documentation: Contains all study documentation including protocol, participant facing documents and data collection tools Study Data Analysis Plan On study completion, this repository will contain a folder with fully anonymised study data once analysis is completed. Data is available under the terms of the CC-BY 4 International license.
